#### **Sample size**

A sample size of 100 infected pregnant women of each asymptomatic and symptomatic group, 1:1 randomly allocated into two study arms, allows to detect an effect size of 30%, 34% and 39% with 80% power and two-tail type-I error of 0.05 assuming 3%, 10% and 30% curation rates in the control group, respectively. In other words, this sample allows detecting differences if the cure rates in the intervention group are at least 33%, 44%, and 69%, respectively. A sample size of 257 non-infected, contact positive, pregnant women per intervention arm will be needed to detect a 3 % reduction in the prevalence of infection with 80% power and two-tail type-I error of 0.05, assuming a prevalence of infection in the control group of 3% after two weeks of follow up.

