The limited information regarding the effects of coronavirus infections during pregnancy results from the epidemics of severe acute respiratory syndrome (SARS) and the Middle East respiratory syndrome (MERS) (12). These two diseases might provide insights into the effects in pregnancy of the new epidemic of coronavirus disease 2019 (COVID-19). The experience with SARS and MERS suggests that both infections are associated with poor maternal and fetal-neonatal outcomes, including severe maternal disease requiring hospitalization, intensive care and ventilator support as well as preterm delivery, IUGR, spontaneous abortion and perinatal death; importantly, the data available indicates that the severity of the disease is worse in pregnant women than in infected non-pregnant women (3). On the other hand, intrauterine maternal-fetal transmission of these two infections has not been documented (3).

Regarding COVID-19, very limited data still exists about its effects in pregnancy. The few reports available of pregnant women infected with COVID-19, all were infected in the third trimester and clinical features were similar to those in non-pregnant adults, with fetal distress and preterm delivery seen in some cases. All women delivered by caesarean section and the newborns tested negative for SARS-CoV-2 (3).

On the other hand, according to the World Health Organisation, there is currently no medication shown to be effective for the treatment or prevention of the SARS-CoV-2 (13).

Early *in-vitro* studies after the SARS 2003 epidemic showed that chloroquine (CQ) had a strong *in-vitro* antiviral effect on SARS-CoV infection of primate cells (14) (13). More recently, an inhibitory *in-vitro* effect of CQ has been shown on the SARS-CoV-2 (15). In addition, *in-vitro* studies comparing CQ with hydroxychloroquine (HCQ) on SARS-CoV-2 infected cells showed that HCQ had a more potent inhibitory effect than CQ (14). These findings led to clinical studies in

China with encouraging results and to include CQ in the recommendations regarding prevention and treatment of the infection in this country (16). In other countries suffering the epidemic (such as Spain) HCQ is currently used to treat admitted patients with SARS-CoV-2 infection. Preliminary unpublished results of a French clinical trial in 24 infected patients showed a clearance of the virus in 75% of those treated with HCQ for 6 days compared with 10% in untreated controls (17)

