#### Trial design

The trial has been designed as a randomized double-blind placebo-controlled multicentre trial to evaluate the safety and efficacy of HCQ to prevent and/or minimize SARS-CoV-2 infection during pregnancy. A total of 714 pregnant women are expected to participate in the study (see sample size calculation).

The study participants will be stratified by clinical presentation and SARS-CoV-2 PCR results. The following are the study groups:

- **SARS-CoV-2-PCR confirmed, infected** pregnant women:
  - a. *symptomatic* (n=100)
  - b. *asymptomatic* (n=100)
- **SARS-CoV-2 PCR negative** pregnant women in **contact** with a SARS-CoV-2-infected confirmed or suspected case (n=514).

Women in each group will be randomly allocated to receive either HCQ or placebo. Evaluations will include safety and tolerability, SARS-CoV-2 PCR and COVID-19 clinical diagnosis and presentation, as well as neonatal SARS-CoV-2 by PCR and IgM/IgG.

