#### **Statistical models and methods of analysis**

The primary analysis of the trial will be:

- The comparison of the proportion of negative SARS-CoV-2 PCR at day 14 after initiating treatment administration among those women who were SARS-CoV-2 PCR positive at recruitment in the ITT and ATP cohorts.
- The comparison of the proportion of pregnant women who were negative SARS-CoV-2 PCR at recruitment and close contacts of confirmed cases of SARS-CoV-2 infection, with a positive PCR for the infection at day 14, in the ITT and ATP cohorts.

Proportions will be compared between the two intervention-arms within each group using the Fisher exact test and presented as relative risk ratio (RR) or reduction of the RR ( $1 - RR * 100\%$ ) if RR lower than 1. Adjustment for co-variables and possible confounders will be done using Poisson regression with a log link and robust estimate of the covariance (Huber method), using the method proposed by Zou et al. 2014 and 2013.

Continuous variables will be compared between groups using Wilcoxon rank sum test and the effect presented as Mean Difference. Adjustment for co-variables and possible cofounders will be done using ordinary least square regression. Variables will be transformed to the logarithm scale if normality is improved and results presented as Proportional Difference. If after transformation, non-normality of the residuals is detected using diagnostic regression plots, robust intervals of confidence and Wald test will be presented instead.

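### The detectable effects stated for the two infected groups correspond to about 25 women per arm, not the planned 50

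*Protocol*

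**What the plan says.** The Sample size section plans "A sample size of 100 infected pregnant women of each asymptomatic and symptomatic group", with equal allocation to HCQ and placebo. It claims that each such group "allows to detect an effect size of 30%, 34% and 39% with 80% power and two-tail type-I error of 0.05". The control cure rates behind these three differences are 3%, 10% and 30%. The section then gives the same claim as treated-arm rates: "this sample allows detecting differences if the cure rates in the intervention group are at least 33%, 44%, and 69%, respectively". The Trial design section confirms 100 symptomatic and 100 asymptomatic infected women.

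Under Statistical models and methods of analysis, each group stands on its own: "Proportions will be compared between the two intervention-arms within each group using the Fisher exact test". Each infected group's power therefore rests on 50 women against 50.

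The Sample size section mentions no allowance for dropout, no continuity correction and no multiplicity adjustment. It does not define cure or say when it is assessed. For the contact group, by contrast, the same section states the follow-up time to which the assumed 3% infection prevalence refers.

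**The concern.** For the stated control rates, differences of 30, 34 and 39 points look too large to be the 80%-power limit with 50 women per arm. If so, the protocol misstates what two of its three groups can detect, and its wording that the treated rate must be at least 33%, 44% or 69% sets the thresholds too high.

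A second, smaller gap is in the same paragraph. The control cure rates have neither a definition nor a time point, so a reader cannot tell whether they describe the outcome that will be analysed. The protocol itself gives two times for that outcome: the Primary endpoint section says day 21, and Statistical models and methods of analysis says day 14.

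**Working it through.** **Inputs (Protocol, Sample size).** 50 per arm in each infected group (100 randomised 1:1); 80% power; two-sided alpha 0.05; pairs 3% vs 33%, 10% vs 44% and 30% vs 69%. Planned test: Fisher exact, within group.

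**Formula.** Pooled two-proportion normal approximation, with p̄ the mean of p1 and p2:

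n per arm = [1.960·√(2p̄(1−p̄)) + 0.842·√(p1(1−p1) + p2(1−p2))]² / (p2−p1)²

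**Step 1: reproduce the protocol's contact-group figure.** For 0% vs 3%, p̄ = 0.015 and n = (0.3369 + 0.1436)² / 0.03² = 0.2309 / 0.0009 = 256.5, which rounds up to the stated 257. With a continuity correction the result is 320. The uncorrected formula therefore appears to be the one the protocol used.

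**Step 2: the same formula for the infected groups.**

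| Pair | p̄ | Numerator | n per arm |
|---|---|---|---|
| 3% vs 33% | 0.18 | (1.0649 + 0.4210)² = 2.208 | 2.208 / 0.0900 = 24.5 |
| 10% vs 44% | 0.27 | (1.2306 + 0.4881)² = 2.954 | 2.954 / 0.1156 = 25.6 |
| 30% vs 69% | 0.495 | (1.3858 + 0.5480)² = 3.740 | 3.740 / 0.1521 = 24.6 |

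Solved the other way, 25 per arm gives detectable treated rates of 32.6%, 44.4% and 68.7%. These round to the printed 33%, 44% and 69%.

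**Step 3: what 50 per arm gives.** The Fisher figures are exact: binomial probabilities summed over all tables with a two-sided p-value of at most 0.05.

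| Control rate | Stated treated rate | Fisher power at the stated pair | 80%-power treated rate, pooled | 80%-power treated rate, Fisher |
|---|---|---|---|---|
| 3% | 33% | 98.3% | 21.0% (18.0 points) | 22.7% (19.7 points) |
| 10% | 44% | 97.0% | 32.7% (22.7 points) | 34.3% (24.3 points) |
| 30% | 69% | 97.3% | 57.5% (27.5 points) | 59.0% (29.0 points) |

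The excess in the stated differences is 30 − 19.7 = 10.3, 34 − 24.3 = 9.7 and 39 − 29.0 = 10.0 points by Fisher. By the pooled formula it is 12.0, 11.3 and 11.5 points.

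**Step 4: can another convention explain 50?** For the three pairs, n per arm is:

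- continuity-corrected: 31, 32, 30
- exact Fisher: about 29-30
- one-sided: 20, 21, 20
- unpooled variance: 22, 23, 22
- arcsine: 21, 25, 25
- 90% power: 33, 34, 33 (continuity-corrected 39, 40, 38)

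None reaches 50. Getting from the continuity-corrected n to 50 would take roughly 40% dropout, which the section does not mention.

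**Step 5: sensitivity to the control rate (assumption only).** The protocol gives no control clearance rate at day 14 or day 21, so this range is illustrative. With Fisher and 50 per arm, control rates of 50%, 70% and 80% would need 78%, 93% and 98% on HCQ. At 85%, even 100% clearance on HCQ gives only 78% power; at 90% it gives 38%.

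**The case against.** The best defence is that nothing in the trial's conduct depends on the error. At the stated control rates the infected groups have more power than claimed. Group sizes, randomisation, endpoint and analysis all stay the same. After the trial, the effects that a null result excludes will be read from the estimate and its confidence interval, not from the planning paragraph. All of this stands, and it makes the point a correction to a stated figure and not a threat to the trial. It does not make the figure right.

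It can also be said that exact limits for 50 per arm remove slack that might have covered losses. That is fair, and the restated text should say that it assumes every woman is evaluable.

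A reader might go further and infer that the control rates are too low for the endpoint, because the Background reports "clearance of the virus in 75% of those treated with HCQ for 6 days compared with 10% in untreated controls" and clearance should be higher by day 21. The protocol does not support that as a finding. The 10% is a preliminary, unpublished figure from a study of 24 infected patients, it is not named as the source of the planning rates, and the paragraph already considers 30%. The day of the primary PCR is itself unsettled. For asymptomatic infected women, the third primary objective is preventing disease, so PCR clearance is not the only reading of cure in that group. What stands is narrower: cure is undefined and the control rates have no time point.

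**Conclusion.** The detectable effects printed for the two infected groups are wrong for the planned sample size. They match about 25 women per arm, while the design has 50. The true 80%-power treated rates are about 23%, 34% and 59% (Fisher), or about 21%, 33% and 57% (pooled), against the printed 33%, 44% and 69%. The stated differences are thus about 10-12 points too large. This assumes 50 evaluable women per arm, two-sided 0.05 and the control rates as printed; at those rates the error is conservative.

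Two stronger readings are not supported. The first is that the infected groups are too small: at the stated differences, their power is 97-98%. The second is that the endpoint will meet a ceiling: that depends on control rates that the protocol does not give. A natural explanation for the factor of two is that 50 was entered as the group total instead of the number per arm, but this is an inference.

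**What to change.** Rewrite the infected-group statement in the Sample size section:

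- Give the detectable HCQ rates for 50 per arm under the planned Fisher test: 22.7%, 34.3% and 59.0% for control rates of 3%, 10% and 30% (differences of 19.7, 24.3 and 29.0 points). Name the method.
- State that these figures assume no loss to follow-up.
- Define cure for each infected group. Tie the control rates to the primary time point once the Primary endpoint section (day 21) and Statistical models and methods of analysis (day 14) have been reconciled.
- Say which control rate is the planning assumption. If higher rates are shown, label them as an assumed sensitivity range: 50%, 70% and 80% would need 78%, 93% and 98% on HCQ, and at 85% or more 80% power cannot be reached.

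The cost is one paragraph of protocol text. Enrolment, randomisation and the planned test stay as they are.

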#### **Study population**

Pregnant women who are undergoing routinely prenatal follow up or attend emergency units at the recruitment hospitals and who report symptoms/signs suggestive of COVID-19 disease or being contact of a suspected or confirmed COVID-19 case.

#### *Inclusion criteria*

Women will be invited to participate in the trial and sign an informed consent if they meet the following inclusion criteria.

- Presenting with fever ( $\geq 37.5^{\circ}\text{C}$ ) and/or one mild symptom suggestive of COVID-19 disease (cough, dyspnoea, chills, odynophagia, diarrhoea, muscle pain, anosmia, taste disorder, headache) OR contact of a SARS-CoV-2 confirmed or suspected case in the past 14 days
- More than 12 weeks of gestation (dated by ultrasonography)
- Agreement to deliver in the study hospitals

#### *Exclusion criteria*

- Known hypersensitivity to HCQ or other 4-aminoquinoline compounds
- History of retinopathy of any aetiology
- Concomitant use of digoxin, cyclosporine, cimetidine

- Known liver disease
- Clinical history of cardiac pathology including known long QT syndrome
- Unable to cooperate with the requirements of the study
- Participating in other intervention studies
- Delivery onset (characterized by painful uterine contractions and variable changes of the cervix, including some degree of effacement and slower progression of dilatation up to 5 cm for first and subsequent labours)

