Chloroquine and HCQ are used in the treatment of systemic lupus erythematosus (SLE) and rheumatoid arthritis (RA) for more than 25 years including in pregnant women (18). The safety of this treatment has been well established during pregnancy. In addition, there is wide evidence of the safety of CQ in the treatment and prevention of malaria in pregnancy in endemic areas (19). Complete rationale for drug selection and dosage are included in Annex 1.

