##### **c) Electrocardiogram**

An electrocardiogram (ECG) will be performed using a mobile device (Kardia®). If the QTc is > than 500 milliseconds the woman will be considered as “study screening failure” and she will not be included in the study. If the QTc is < than 500 ms the recruitment procedures will continue.

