#### **b) Treatment arm allocation**

Participants will be then randomized in a 1:1 ratio to HCQ (400 mg/day for three days, followed by 200 mg/day for 11 days) or placebo (2 tablets for three days, followed by one tablet for 11 days).

Allocation of participants to study arms will be done centrally by the trial's Sponsor (the Barcelona Institute for Global Health, ISGlobal) by block randomization. This method will ensure balanced allocation to both arms. The electronic CRF will assign automatically a study number to each participant, depending on her study group and recruitment site. Each number will be related to a treatment number, which assigns them to one of the study arms. Randomizations lists with treatment assignment for each study participant will be concealed in opaque sealed envelopes and only open in case of urgent need following study unblinding procedures.

A study card will be given to the participant in order to facilitate their clinical management in case they attend primary care centres or other hospitals.

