#### **Administration of study drugs**

Study tablets will be identically packaged in small opaque bottles. All study personnel, investigators and the participants will remain blinded throughout the trial.

Participants will receive a bottle containing 19 tablets of study medication. They will be instructed to take two tablets for first three days and one tablet for the following 11 days. The first day of treatment, drug administration will be supervised.

Women vomiting within the first 30 minutes of drug administration will be given a second full drug dose; women vomiting after 30-60 minutes of study tablets administration will be given an additional half dose of the drug.

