#### **Follow-up and assessment of treatment adherence**

Participants will be contacted by phone daily during the intervention period by study personnel to assess general health condition, as well as the drugs' tolerability and potential adverse events. Treatment adherence and the intake of any concomitant medication will be also requested daily. Information regarding any unscheduled study visit to the hospital will be registered.

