#### **e. Safety**

The study is designed as a clinical trial in which pregnant women followed up prospectively from the antenatal care clinic contact until the end of pregnancy and their newborns for the first 24 hours of life.

Drug exposure to any drug during pregnancy may carry risks to both the mother and the developing foetus (28). Chloroquine and HCQ are on the WHO Essential Medicines List for use in rheumatic disorders, and is widely prescribed as an anti-inflammatory for rheumatoid arthritis (RA), systemic lupus erythematosus (SLE), and other autoimmune syndromes for more than 25 years including in pregnant women (18). Therefore, the safety of this treatment has been well established during pregnancy. In addition, there is wide evidence of the safety of CQ in the treatment and prevention of malaria in pregnancy in endemic areas (19). HCQ is associated with a better safety profile for daily and chronic use than CQ. Based on the limited *in vitro* data available, HCQ appears to be slightly more potent than CQ against SARS-CoV-2 (15).

With tens of millions of doses administered for malaria and autoimmune diseases, the side effect profile of HCQ is well described and the drug is generally well tolerated.

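### The exclusion criteria do not bar current hydroxychloroquine or chloroquine use, so a woman already on the drug can be randomised and given the blinded course on top of it

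*Protocol*

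**What the plan says.** In the Exclusion criteria (section 5.a), HCQ appears once, as an allergy: "Known hypersensitivity to HCQ or other 4-aminoquinoline compounds". The one line that excludes on current medication is "Concomitant use of digoxin, cyclosporine, cimetidine". The remaining lines cover retinopathy, liver disease, cardiac pathology including long QT, inability to cooperate, other intervention studies and onset of labour. The inclusion criteria concern symptoms or contact, gestational age and place of delivery.

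The Background says that CQ and HCQ are "used in the treatment of systemic lupus erythematosus (SLE) and rheumatoid arthritis (RA) for more than 25 years including in pregnant women", and section 5.e (Safety) repeats this. The Background also says that Spanish hospitals were already giving HCQ to inpatients with SARS-CoV-2 infection.

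At screening, a QTc above 500 ms is a screening failure; otherwise, "If the QTc is < than 500 ms the recruitment procedures will continue". The woman is then randomised 1:1, and "All study personnel, investigators and the participants will remain blinded throughout the trial". During the course, "the intake of any concomitant medication will be also requested daily". Table 1 also has concomitant medication recorded at enrolment. It schedules ECGs at enrolment and at the visit seven days after the course ends, and at no point between.

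**The concern.** The protocol rests part of its safety case on pregnant women who take the study drug for autoimmune disease, yet it does not say what happens when one of them is screened. A stable user who tolerates the drug and has none of the listed conditions meets the criteria.

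If allocated to HCQ, she takes two supplies of the same drug during pregnancy, one of them blinded. If allocated to placebo, she is counted as a control while taking HCQ, and the safety analysis is by trial arm. The same stacking can arise after enrolment if a participant is admitted and given open-label HCQ.

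What is at stake is avoidable extra exposure for a small and unknown number of women. The trial's efficacy conclusion is not at stake.

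**Working it through.** **Step 1. Does any safeguard in the protocol close the gap?**

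- *Other exclusions.* Retinopathy, liver disease or cardiac pathology would remove some long-term users, but not one who has none of these. The other-trial exclusion does not reach a routine prescription.
- *Screening ECG.* It removes a woman already above 500 ms. It is taken on her own dose alone, so it does not test the combined dose.
- *Later ECG.* The only one scheduled is at day 21, after the 14-day course has ended. Section 5.b also calls a QTc rise of 25% or more from baseline abnormal, but her baseline would be an on-drug value.
- *Medication recording.* It is done at enrolment and daily, so her use could be seen before or during treatment. No text says what follows from a positive answer. Table 1 lists concomitant medication without saying that dose is recorded.
- *Supervised first dose, adverse-event actions, urgent unblinding.* Each allows someone to step in. None requires it because of HCQ or CQ use.

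The gap stays open in the text available.

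**Step 2. Added dose**

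From the protocol: 400 mg/day for 3 days, then 200 mg/day for 11 days. Study course = 3 × 400 + 11 × 200 = 3,400 mg.

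Her own dose is not in the documents. Assume 200 to 400 mg/day:

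| Assumed own dose | Days 1–3 | Days 4–14 | 14-day total | Ratio to study course |
|---|---|---|---|---|
| 200 mg/day | 600 mg/day | 400 mg/day | 3,400 + 14 × 200 = 6,200 mg | 1.8 |
| 400 mg/day | 800 mg/day | 600 mg/day | 3,400 + 14 × 400 = 9,000 mg | 2.6 |

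On these assumed doses she is at or above the study's 400 mg/day loading level on all 14 days. Section 5.e gives the short loading phase as the way to avoid rash.

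**Step 3. How many women**

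The HCQ arm has 714 / 2 = 357 women. The share p of current users is not in the documents. The expected number in that arm is 357p, and the chance of at least one is 1 − (1 − p)^357.

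| Assumed p | Expected in HCQ arm | Chance of at least one |
|---|---|---|
| 0 | 0 | 0% |
| 0.01% | 0.04 | 3.5% |
| 0.1% | 0.36 | 30% |
| 0.5% | 1.79 | 83% |

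The result follows the assumed p almost entirely, so the documents support no particular value.

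**Step 4. Effect on power, uninfected contacts**

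The plan's figure: 3% infected on control, a 3-point reduction (hence 0% on HCQ), two-sided 0.05, 80% power. The pooled-variance formula without continuity correction is n = [1.96√(2p̄(1−p̄)) + 0.842√(p₁(1−p₁) + p₂(1−p₂))]² / (p₁−p₂)². With p₁ = 0.03, p₂ = 0 and p̄ = 0.015, n = (0.337 + 0.144)² / 0.0009 ≈ 257 per arm. This reproduces the plan, with power 80.1%.

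Suppose a share f of women in both arms take HCQ whatever their allocation, with the full planned effect. The control rate becomes 0.03(1 − f), against 0.

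| f | Power at 257 per arm | n per arm for 80% |
|---|---|---|
| 0.1% | 80.0% | 257 |
| 1% | 79.7% | 260 |
| 2% | 79.3% | 262 |
| 5% | 78.0% | 271 |

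Even at 5%, the loss is about 2 points.

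**The case against.** The strongest case against is about weight. Prevalence and own dose are both assumed, so any probability or dose multiple only restates the assumptions. That stands: a reader might infer from Step 3 that a double-dosed participant is likely, and the documents do not support this.

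A reader might also infer harm. The protocol gives no harmful dose threshold and regards HCQ as well established in pregnancy. Its remark that long-term toxicities are unlikely concerns the two-week study course alone, so it neither shows harm from combined dosing nor rules it out.

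It would be too strong to say that the eligibility list is the only thing that could prevent stacking. The investigator has the medical history and medication record at enrolment, and the first dose is supervised, so a careful site may notice and decline her. What remains is that the criteria do not tell the site to do so.

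The annexes, operating procedures and consent form are not available here, and a restriction could sit there. Section 5.e does place cautions outside the exclusion list (bone marrow disorders, glucose-lowering drugs). None of them concerns current HCQ or CQ use, and the exclusion list refers to no annex.

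Finally, an extra exclusion line does nothing about open-label HCQ started after enrolment. That is correct, and it is why the remedy has two parts.

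**Conclusion.** The point holds as a low-frequency participant-safety gap. Followed as written, the eligibility rule admits a current HCQ or CQ user with QTc below 500 ms, and nothing in the protocol body requires anyone to withhold or stop the blinded drug.

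The firm figure is the 3,400 mg study course. The 14-day combined total of 6,200 to 9,000 mg depends on an assumed own dose of 200 to 400 mg/day. The number of such women is unknown and may be zero. This is added exposure, with no harm demonstrated.

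A reader might infer that placebo-arm users undermine the efficacy comparison. The calculation does not support that: power for the contact group falls from 80.1% to 79.7% at 1% users and to 78.0% at 5%. The change is worth making because it is cheap and specific.

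**What to change.** Two changes to the protocol:

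1. In the Exclusion criteria, extend the line that bars digoxin, cyclosporine and cimetidine by adding *hydroxychloroquine, chloroquine or another 4-aminoquinoline*.
2. After the section on follow-up and treatment adherence, state that blinded study drug stops if open-label HCQ or CQ is prescribed during the 14-day course, and that the woman stays in follow-up and in the intention-to-treat analysis.

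Concomitant medication is already collected at enrolment and daily, so no new visit, data field or sample size is needed. The cost is that a few long-term users become ineligible. A woman whose study drug is stopped early also leaves the according-to-protocol population, which requires the full 14 days.
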